##### Longitudinal Analyses

The time-to-event analyses including Kaplan-Meier survival curves, log-rank tests, and Cox proportional hazards regression models will be used to assess whether unique grEEG patterns predict a decline in CdF longitudinally.

##### Power Analysis

With the sample size of 180 older adults who are cognitively unimpaired, we estimate that there will be 54 individuals classified with CdF limitations based on our preliminary studies. With a significance level (α) of .05, using a 2-sided 2-sample *t* test, this study achieves 80% power to detect a minimal difference of 0.5 SD in the grEEG measure between CdF limitation groups. The minimum detectable hazards ratio for CdF decline between older adults with and without unique grEEG pattern ranges from 1.52 to 1.69 (assuming event rate between 0.30 and 0.48) with a power of 0.8 and a 2-sided type I error rate of 5% [89].

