#### Prevalence of Unique grEEG Activation

To estimate the prevalence of grEEG abnormalities in aging, we reanalyzed previously published data [16]. Using event-related potentials measured in control participants (ie, young adults), we defined a threshold (1.5 SD from the mean 2.2 µV) to calculate the percentage of unique grEEG (event-related potential, ERP_young_>1.5 SD, mean 2.2 µV) in older participants. The prevalence of grEEG abnormality in older adults was 25% (4 out of 16).

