### Aim 2—Determine Association of Dementia-Related Pathology With Incidence of Neural Signature of CdF

#### Overview

Figure 6 shows preliminary findings in support of our hypothesis that Aβ burden [90] as well as MRI-regions impacted early during AD and cerebrovascular pathology are nominally associated with the presence of unique grEEG activation. Figure 6 shows the volume and white matter differences in brain regions between participants with and without unique grEEG patterns during DTW (15/28). Further, when grouping participants in tertiles based on amyloid probability score (APS) [90]—APS accounts for Aβ 42/40 ratio, age, and *ApoE* phenotype - we find that high APS is nominally associated with the increased presence of unique grEEG activation (1st tertile: 1 out of 5; 2nd tertile: 3 out of 6; 3rd tertile: 3 out of 5).

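### The Aim 1 minimum detectable hazard ratio of 1.52 to 1.69 for CdF decline cannot hold for the with/without-signature contrast it names in 180 participants

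*Protocol article*

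**What the plan says.** Under Statistical Plan Aim 1, the Longitudinal Analyses paragraph says of the CdF outcome that "Kaplan-Meier survival curves, log-rank tests, and Cox proportional hazards regression models will be used to assess whether unique grEEG patterns predict a decline". Survival curves and log-rank tests compare groups, so the exposure there is the presence or absence of the pattern.

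The Power Analysis paragraph opens "With the sample size of 180 older adults who are cognitively unimpaired". It then gives the detectable effect for this analysis: "The minimum detectable hazards ratio for CdF decline between older adults with and without unique grEEG pattern ranges from 1.52 to 1.69". The stated conditions are an event rate of 0.30 to 0.48, 80% power and a two-sided 5% error rate.

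The paragraph cites a reference for the method. It gives no formula, no share of participants with the pattern, no attrition and no baseline exclusions for this calculation. Nothing describes the hazard ratio as per SD. Elsewhere the article offers two candidate shares: 25% (4 of 16, Prevalence of Unique grEEG Activation) and 15 of 28 (Aim 2 Overview).

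**The concern.** The article's Hypothesis section makes prediction of later CdF decline by the signature a central claim, and this sentence is the power statement for it. A reader learns that a hazard 52% to 69% higher in people with the pattern would be detected four times in five. The expected events, 54 to 86 if all 180 are analysed, look too few for a two-group comparison at those hazard ratios. If so, the study has about an even chance or less of detecting an effect of that size, and a null result could be given more weight than it deserves.

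**Working it through.** **Inputs.** N = 180, event rates 0.30 and 0.48, hazard ratios 1.69 and 1.52, power 0.80, two-sided 5% (all from the Aim 1 Power Analysis). The larger hazard ratio is paired with the smaller event rate. The event rate is read as the cumulative proportion with an event, so D = 180 × 0.30 = 54 or 180 × 0.48 = 86.4 events.

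**Formula.** For a Cox or log-rank comparison, ln(HR) = (1.960 + 0.842)/√(D × V). For a yes/no exposure with share p, V = p(1 − p), which is at most 0.25. For a continuous predictor with the hazard ratio per SD, V = 1.

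**1. Can the printed figures be reproduced as a two-group contrast?** The required D × V is 7.849/[ln(HR)]².
- HR 1.69: 7.849/0.2753 = 28.5, so V = 28.5/54 = 0.53.
- HR 1.52: 7.849/0.1753 = 44.8, so V = 44.8/86.4 = 0.52.

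Both are more than twice the maximum of 0.25, so the figures cannot be reproduced at any p. At 50:50 the events needed are 28.5/0.25 = 114.0 and 44.8/0.25 = 179.1, that is 115 and 180 after rounding up, against 54 and 86 expected. That corresponds to roughly 373 to 380 participants.

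**2. Power at the printed hazard ratios**, as Φ(√(D × V) × ln(HR) − 1.96), with 180 analysed and 50:50:
- HR 1.69, 54 events: √13.5 × 0.525 − 1.96 = −0.03, power 48.7%.
- HR 1.52, 86.4 events: √21.6 × 0.419 − 1.96 = −0.01, power 49.4%.

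A log-rank simulation (6,000 runs per setting) gives 47% and 49% at 50:50, and 49% and 50% at 40:60.

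**3. Two-group detectable hazard ratio at 80% power:**

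| Analysed | Share with pattern | Rate 0.48 | Rate 0.30 |
|---|---|---|---|
| 180 | 50% | 1.83 | 2.14 |
| 180 | 15/28 | 1.83 | 2.15 |
| 180 | 25% | 2.01 | 2.41 |
| 144 (20% attrition) | 50% | 1.96 | 2.35 |
| 144 (20% attrition) | 25% | 2.18 | 2.68 |

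Simulated power at 2.14 and 1.83 (180 analysed, 50:50) is 79% in both cases, so the best-case row is sound.

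**4. Other ways to reach the printed range.** One-sided 5% testing at 50:50 gives 61% and 62% power. Freedman's formula needs 120 and 185 events. Pairing HR 1.69 with the higher rate of 0.48 gives √21.6 × 0.525 − 1.96 = 0.48, or 68%. None reaches 80%.

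**5. Where the figures may come from.** The printed values fix only the product N × V: 28.5/0.30 = 95.0 and 44.8/0.48 = 93.3. Allowing for rounding of the hazard ratios these are 94.0 to 96.1 and 91.8 to 94.8, so one value between 94.0 and 94.8 serves both ends. With V = 1 and N = 94.5, the formula gives 1.69 and 1.52; at an event rate of 0.25 it gives 1.78, the Aim 3 figure. With V = 1 and N = 180 it gives 1.35 to 1.46, and with N = 144 it gives 1.40 to 1.53.

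**The case against.** **The event rate is not defined.** Read as an annual rate over the four-year maximum in the Outcomes section, with 180 analysed at 50:50, power would be about 84% to 87% for HR 1.69 and 74% to 77% for HR 1.52. This is the best defence, but it does not reproduce the statement: the detectable range becomes 1.57 to 1.65, or 1.54 to 1.62, depending on how the annual rate is converted. The information implied at the two ends also has a ratio of 44.8/28.5 = 1.57. Cumulative proportions predict 0.48/0.30 = 1.6, which agrees within rounding. What stands is that the 49% to 50% is conditional on the cumulative reading.

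**The formula used is unknown.** A reader might infer that the authors certainly used a per-SD formula. The article does not support that. It names no formula and no N of 94.5, and a product of 94.5 would equally arise from 378 people split 50:50 (378 × 0.25). The match with Aim 3 makes the per-SD explanation plausible, not established. The inconsistency does not depend on it.

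**Power might be put lower still.** With 25% carrying the pattern, the formula gives 39% with 180 analysed and 32% with 144. These should not be pressed. Simulation gives about 44% to 45% and 38% to 39%. The 25% also comes from an event-related-potential cut-off set in young adults, whereas the signature under Neural Signature of CdF uses median splits of θ and β source activity. The 20% attrition is stated for Aim 2 only.

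**The scope is limited.** The paragraph headed Primary Analyses for Aim 1 covers t tests and correlations. The t-test statement passes: 54 against 126 at 0.5 SD has 86% power. Nothing shows that 180 was derived from the hazard ratio. Both points are correct and confine the concern to the longitudinal claim, which is still a central hypothesis.

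**Conclusion.** The concern holds for the printed sentence. A minimum detectable hazard ratio of 1.52 to 1.69 is not attainable for pattern present versus absent among 180 people at the stated event rates, power and error rate. This conclusion needs no assumption about the share with the pattern. It does rest on reading the event rate as a cumulative proportion, which fits the printed figures better than an annual rate.

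On that reading, with all 180 analysed, power at the printed values is about 49% to 50% at best, and the detectable hazard ratio is 1.83 to 2.14 at an even split. Attrition, exclusion of the 54 people expected to have CdF limitations at baseline (the article does not say whether they leave the risk set), or a 25% share would each raise it. A per-SD origin remains an inference. The Aim 1 t-test power is not affected.

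**What to change.** Recompute and restate the two-group detectable hazard ratio for the number actually analysed. State with it the assumed share with the pattern, attrition, any baseline exclusions, and whether the event rate is cumulative or annual. With a cumulative rate, about 1.8 to 2.1 is the best case and applies only if all 180 are analysed at a near-even split; it should not be adopted as a default.

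Alternatively, if a continuous grEEG measure was intended, name it as the Cox predictor in Longitudinal Analyses, label the hazard ratio 'per 1 SD' and give the analysed N. The figure would be 1.35 to 1.46 with 180 and 1.40 to 1.53 with 144; the printed 1.52 to 1.69 would need about 94 to 95 analysed.

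The Aim 3 figure should be checked in the same pass, since the same form returns it. The cost is wording and one recalculation, with a less favourable or relabelled figure. No extra participants or procedures are needed.

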### Aim 2—Determine Association of Dementia-Related Pathology With Incidence of Neural Signature of CdF

#### Overview

Figure 6 shows preliminary findings in support of our hypothesis that Aβ burden [90] as well as MRI-regions impacted early during AD and cerebrovascular pathology are nominally associated with the presence of unique grEEG activation. Figure 6 shows the volume and white matter differences in brain regions between participants with and without unique grEEG patterns during DTW (15/28). Further, when grouping participants in tertiles based on amyloid probability score (APS) [90]—APS accounts for Aβ 42/40 ratio, age, and *ApoE* phenotype - we find that high APS is nominally associated with the increased presence of unique grEEG activation (1st tertile: 1 out of 5; 2nd tertile: 3 out of 6; 3rd tertile: 3 out of 5).

**Figure 6 figure6:**
[figure not shown]
Individuals with unique grEEG pattern have smaller cuneus, lingual, ant. cingulate, and increased white matter burden of the fimbra, which connects the hippocampus. Act.: activity; ant.: anterior; Anteri.: anterior; grEEG: gait-related electroencephalographic; MRI: magnetic resonance imaging; WMH: white matter hyperintensities.

#### MRI Image Acquisition

All images will be acquired at the Gruss Magnetic Resonance Research Center at Einstein, using a Philips 3T Elition multinuclear MRI/magnetic resonance spectroscopy system. Our noninvasive MRI imaging procedures are reliable and extensively used in aging and dementia studies. T1-weighted images will be acquired using axial 3D-magnetization-prepared rapid acquisition with gradient echo parameters over a 240 mm field of view; 1.0 mm isotropic resolution, echo time/repetition time=4.6/9.9 ms, α= 8o, and SENSE factor 2.6. 3D-FLAIR images will be acquired with repetition time/inversion time=4800/1650 ms, echo time=335 ms, 240 × 238 acquisition matrix, and 0.46 mm voxel size. Functional (resting-state and task-based), diffusion-weighted, arterial spin labeling, and susceptibility-weighted images will also be acquired as part of the parent study (for additional details see [32]). A radiologist will review each MRI scan and confirm that there are no clinically significant findings for any of the participants. WMH will be quantified from 3D-FLAIR using the lesion segmentation toolbox [91] (implemented with SPM12/MatLab). T1-weighted images will be reconstructed using FreeSurfer (version 7.2; FreeSurfer). FreeSurfer’s subcortical segmentation and cortical parcellation are comparable to manual labeling [92]. Parcellation of the T1-weighted data into anatomical brain regions is important for examining cortical thickness and volume associated with the grEEG pattern during visually perturbed walking or dual-task walking. Gray matter volumes and cortical thicknesses of 68 cortical regions will be extracted from this pipeline and entered into subsequent statistical models.

#### Statistical Plan Aim 2

##### Primary Analyses

The time-to-event analyses will be used to assess whether Aβ and WMH predict the incidence of the neural signature of CdF. Prevalent cases—that is, older adults with the unique grEEG pattern at baseline—will be excluded. Time to the neural signature will be defined as the time interval between baseline and the date when the participant demonstrates the unique grEEG pattern during the longitudinal follow-up.

##### Power Analysis

Preclinical Aβ/WMH prevalence is estimated at 24% to 45% among older adults who are cognitively unimpaired [93-95]. With a baseline sample size of 180 and a conservative attrition rate of 20%, the minimum detectable hazards ratio for incident neural signature of CdF between older adults with and without dementia-related pathology is 1.75 (assuming an event rate of 0.25) with a statistical power of 80% and a 2-sided type I error rate of 5%.

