##### Power Analysis

The minimum detectable hazards ratio for incident neural signature of CdF between older adults with less physical activity and normal level physical activity is 1.78 (assuming an event rate of 0.25) with a power of 0.8 and a 2-sided type I error rate of 5%.

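### The minimum detectable hazard ratios for the incident neural signature (1.75 in Aim 2, 1.78 in Aim 3) do not hold for the two-group contrasts they describe; they are probably per-SD figures mislabelled

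*Protocol article*

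**What the plan says.** The power analysis for Aim 2 starts from an exposure prevalence: "Preclinical Aβ/WMH prevalence is estimated at 24% to 45% among older adults who are cognitively unimpaired". It then sets the sample: "With a baseline sample size of 180 and a conservative attrition rate of 20"%. The detectable hazard ratio for the incident signature is given "between older adults with and without dementia-related pathology is 1.75 (assuming an event rate of 0.25"). Power is set at 80% and the two-sided error rate at 5%.

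The power analysis for Aim 3 gives the hazard ratio "between older adults with less physical activity and normal level physical activity is 1.78 (assuming an event rate of 0.25"), with the same power and type I error. It states neither the share of less active participants nor any attrition.

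The Primary Analyses paragraph for Aim 2 restricts the risk set: "Prevalent cases—that is, older adults with the unique grEEG pattern at baseline—will be excluded". Two pilot figures bear on how many that might be. The section on prevalence of unique grEEG activation reports: "The prevalence of grEEG abnormality in older adults was 25% (4 out of 16"). The Aim 2 overview compares "participants with and without unique grEEG patterns during DTW (15/28").

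**The concern.** Both sentences compare two groups, and the Aim 2 paragraph opens with the proportion exposed, an input that is needed only for a yes/no contrast. For such a contrast, precision depends on the number of events and on p(1−p), which cannot exceed 0.25. A sample of 180 with a quarter having the event gives 45 events at most, which is few for detecting a hazard ratio near 1.75.

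If the figures are taken as worded, a null comparison of pathology or activity groups could be read as evidence against moderate effects when the study had well under 80% power to see them.

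**Working it through.** **Inputs.** Power 0.80, two-sided alpha 0.05 and event rate 0.25 (both power analyses). N = 180, attrition 20% and exposure prevalence p = 0.24 to 0.45 (Aim 2). The Aim 3 split is not given, so p = 0.5 is assumed as the most favourable case.

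**Formulas (Schoenfeld).** Events needed: D = (1.960 + 0.8416)² / [p(1−p)(ln HR)²] = 7.849 / [p(1−p)(ln HR)²]. Inverted: detectable HR = exp{2.8016 / √[D·p(1−p)]}.

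**Events needed for the stated values**

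| HR | p | Calculation | Events |
|---|---|---|---|
| 1.75 | 0.50 | 7.849 / (0.25 × 0.3132) | 100.3 |
| 1.75 | 0.45 | 7.849 / (0.2475 × 0.3132) | 101.3 |
| 1.75 | 0.24 | 7.849 / (0.1824 × 0.3132) | 137.4 |
| 1.78 | 0.50 | 7.849 / (0.25 × 0.3325) | 94.4 |

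**Events available and what they detect in a two-group contrast**

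| Risk set | Events | Detectable HR, p = 0.45 to 0.24 | Detectable HR, p = 0.5 | Power for 1.75, p = 0.24 to 0.45 | Power for 1.78, p = 0.5 |
|---|---|---|---|---|---|
| 180, no losses | 45 | 2.32 to 2.66 | 2.31 | 36% to 46% | 49% |
| 180 × 0.8 = 144 | 36 | 2.56 to 2.98 | 2.54 | 30% to 39% | 41% |
| 144 × 0.75 = 108 (assumes 25% prevalent cases) | 27 | 2.96 to 3.53 | 2.94 | 24% to 30% | 32% |

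The first two rows use only stated inputs, apart from the Aim 3 split. The third row borrows the 25% from an event-related potential threshold applied to 16 older adults. That is not the theta/beta pattern that defines the signature, so the row is a scenario.

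**Reproducing the plan's figures.** They do not come out of the two-group formula, but they do come out if p(1−p) is replaced by 1, that is, for a hazard ratio per SD of a continuous covariate: HR = exp(2.8016 / √D).

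- Aim 2: 25.2 events (N = 100.8 × 0.25) gives 1.747, against 1.75 stated.
- Aim 3: 23.6 events (N = 94.5 × 0.25) gives 1.780, against 1.78 stated.
- Aim 1, same N = 94.5: event rate 0.48 gives 1.516 and 0.30 gives 1.692, against 1.52 and 1.69 stated.

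All four figures fit. The two risk sets were found by working backwards; the article does not state them.

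**Other readings tried**

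- One-sided alpha still needs at least 79 events for 1.75 and 75 for 1.78.
- Taking 0.25 as the rate in the unexposed group gives at most about 59 events with all 180, and power below 60%.
- Taking 0.25 as an annual rate over four years gives 144 × (1 − 0.75⁴) = 98 events. The detectable HR is then 1.76 at p = 0.45 but 1.94 at p = 0.24. Removing 25% as prevalent cases leaves 74 events and 1.93 to 2.15.

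**The case against.** The strongest reply is that nothing is wrong with the underlying calculation. The Aim 2 analysis paragraph asks whether amyloid and WMH predict incidence and does not dichotomise them; the Aim 3 paragraph speaks of physical activity at baseline. If the exposures enter as continuous standardised variables, 1.75 and 1.78 are attainable, and 27 events would even detect 1.71. This largely stands, and it rules out saying that the hazard ratios cannot be reached or that the aims are necessarily underpowered. It does not rescue the sentences as written. They describe groups, one of them rests on a prevalence, and neither says per SD. The article also classifies cognitively unimpaired participants as amyloid-positive or not, so a group analysis is a natural reading.

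A reader might also infer that the exclusion of prevalent cases was forgotten, because only attrition is named. The documents do not support that. The risk set of about 100.8 that reproduces 1.75 equals 180 × 0.8 × 0.7, which would mean a deduction beyond attrition had been made. That factor is itself inferred, so the point cannot be settled either way.

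Nor should 15/28 be used as a baseline prevalence to push the events down to about 17 and the detectable hazard ratio to 4 or 5. The section defining the signature shows that the pilot groups came from median splits, so a share near one half is largely built in. The text also does not make clear that 15 is the number with the pattern.

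The annual-rate reading comes close in one corner, but the text does not say annual. It misses at the plan's own lower prevalence, and it fails once prevalent cases are removed.

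**Conclusion.** The stated hazard ratios do not match the two-group wording. On the plan's own inputs the Aim 2 contrast can detect about 2.3–2.7 with no losses and about 2.6–3.0 after attrition, against 1.75 stated. Power for 1.75 is 36–46% and 30–39% respectively, against 80% stated. For Aim 3 the detectable value is at best 2.3 (45 events) or 2.5 (36 events), against 1.78; the 50:50 split is an assumption, and any other split is worse. This much needs no assumption about prevalent cases. Excluding them moves the detectable value to roughly 2.9–3.5 across both aims if 25% prevalence is assumed.

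The most likely explanation is that per-SD hazard ratios were described as group contrasts. That rests on the fit to all four stated values, with risk sets that are inferred. The finding is therefore a wrong description of what the study can detect. It does not show that Aims 2 and 3 lack power under a continuous analysis.

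**What to change.** In both power paragraphs, state the number at risk and the expected events after attrition and after removal of prevalent cases, with the assumed baseline prevalence of the signature, and say that 0.25 is cumulative over follow-up if that is meant. Then choose one of two routes.

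1. Declare the Aβ42/40 ratio, WMH and physical activity as continuous standardised exposures in the primary models, and label the hazard ratio per SD. With 36 events this is exp(2.8016/√36) = 1.60; with 27 events, exp(2.8016/√27) = 1.71.
2. Keep the two-group contrasts and restate the detectable hazard ratio: at least about 2.5–3.0 after attrition, and about 3 or more after prevalent cases are removed. For Aim 3, give the expected split and mark 50:50 as a best case.

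The cost is two rewritten paragraphs, with no added participants or procedures. The stated figures become less favourable only under the second route.

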### Aim 3: Establish Associations Between Physical Inactivity and Neural Signature of CdF

#### Overview

Figure 7 shows preliminary findings in support of our prediction that less exercise (assessed with the Late Life Function and Disability Instrument [96,97]) is nominally associated with 13-28 Hz less desynchronization during DTW.

**Figure 7 figure7:**
[figure not shown]
Less exercise is related to less β desynchronization during DTW. DTW: dual-task walking; W: walking.

#### Statistical Plan Aim 3

##### Overview

The time-to-event analysis will be used to assess whether physical activity at baseline predicts the presence of the neural signature of CdF longitudinally.

##### Power Analysis

The minimum detectable hazards ratio for incident neural signature of CdF between older adults with less physical activity and normal level physical activity is 1.78 (assuming an event rate of 0.25) with a power of 0.8 and a 2-sided type I error rate of 5%.

## Discussion

### Principal Findings

A major effort aimed at curbing the rapid rise of dementia revolves around early intervention. To substantiate early intervention, it is crucial to enhance the accuracy of early detection. We focus on the neural signature of early limitations in CdF to improve detection. Walking is central to many instrumental and complex activities [9,10]. To determine the neural signature of CdF, our team [11-19] and others [73,87,98-104] have established the validity and reliability of neurophysiological recordings while participants are in motion. We designed novel grEEG protocols for this proposal and selected walking as an activity that, compared to other daily activities (eg, preparing a meal), allows for the use of standardized, reproducible, reliable, and well-tolerated study protocols across participants [30,39,105,106].

Our preliminary findings in 28 older adults without MCI/dementia show that reporting of CdF limitations is associated with a unique grEEG activation pattern: 13-28 Hz central gyrus desynchronization paired with 3-7 Hz fronto-medial synchronization. We term this electroencephalographic activation pattern the neural signature of CdF. This subsample also had higher Aβ burden, smaller brain volume, and WMH in regions affected early by dementia and engaged in less physical exercise.

Some limitations are important to note. The ceiling effect with a majority reporting no limitations in CdF is a concern (eg, in Marshall et al [79] study only 16% reported limitations). However, in our study, 30% of individuals reported limitations [1]. To optimize detection, we choose 2 validated and reliable instruments (self-report [107] and paper-pencil test [35] with numerous dependent variables such as self-assessment, time-to-complete, and number and type of errors to quantify performance) covering a broad range of complex daily activities. Further, different processes denoted by Aβ deposition and WMH and their respective roles in the etiology of AD and other dementias are matters of ongoing debates. The prevalence of amyloid deposition in normal aging warrants consideration of Aβ in concert with phosphorylated τ and neurofilament light assays to recognize the multitude and temporal order of pathological processes leading up to clinical signs.

In summary, establishing a noninvasive neurophysiological signature of prevalence and incidence of CdF decline will refine pre-MCI stage characterization. As our recent study shows [1], both individuals who progress and do not progress to MCI may report mild limitations in CdF during the preclinical period, though more limitations are reported in the individuals who go on to develop MCI. By establishing the clinical relevance and biological basis of the neural signature of CdF decline, we aim to improve prediction during preclinical stages of ADs and other dementias.

